## Abstract

**Background:**

Despite Australia’s sunny climate, low vitamin D levels are increasingly prevalent. Sun exposure is limited by long working hours, an increase in time spent indoors, and sun protection practices, and there is limited dietary vitamin D fortification. While the importance of vitamin D for bone mineralization is well known, its role as a protective agent against chronic diseases, such as type 2 diabetes and cardiovascular disease, is less understood. Observational and limited intervention studies suggest that vitamin D might improve insulin sensitivity and secretion, mainly via its anti-inflammatory properties, thereby decreasing the risk of development and progression of type 2 diabetes. The primary aim of this trial is to investigate whether improved plasma concentrations of 25-hydroxyvitamin D (25(OH)D), obtained through vitamin D supplementation, will increase insulin sensitivity and insulin secretion. A secondary aim is to determine whether these relationships are mediated by a reduction in underlying subclinical inflammation associated with obesity.

**Methods/Design:**

Fifty overweight but otherwise healthy nondiabetic adults between 18 and 60 years old, with low vitamin D levels (25(OH)D < 50 nmol/l), will be randomly assigned to intervention or placebo. At baseline, participants will undergo a medical review and anthropometric measurements, including dual X-ray absorptiometry, an intravenous glucose tolerance test, muscle and fat biopsies, a hyperinsulinemic euglycemic clamp, and questionnaires assessing diet, physical activity, sun exposure, back and knee pain, and depression. The intervention group will receive a first dose of 100,000 IU followed by 4,000 IU vitamin D (cholecalciferol) daily, while the placebo group will receive apparently identical capsules, both for a period of 16 weeks. All measurements will be repeated at follow-up, with the primary outcome measure expressed as a change from baseline in insulin sensitivity and secretion for the intervention group compared with the placebo group. Secondary outcome measures will compare changes in anthropometry, cardiovascular risk factors, and inflammatory markers.

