### Sample size calculation

Based on data from a similar healthy cohort of overweight or obese subjects in our metabolic laboratory, with a mean (standard deviation) insulin-mediated glucose uptake value of 8.1 (2.0) mg glucose per kg per minute, a sample size of 25 completing each arm is required to detect a 20 % change in insulin-mediated glucose uptake between treatment group and placebo. The 20 % increase is based on results from a study indicating the effect of vitamin D supplementation in subjects with diabetes using a comparable insulin sensitivity measurement technique and 4 weeks’ treatment [36]. Based on a type I error of 0.05 (two-tail) and a type II error of 0.20 (power = 80 %), we would require 50 participants to complete the trial.

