### Outcome measurements

The primary outcome measure in this trial is the difference (change) in insulin sensitivity between the vitamin D and placebo groups. Secondary outcome measures include changes in insulin secretion, weight, body mass index, waist, waist to hip ratio, resting systolic and diastolic blood pressure, lipid profile, and markers of inflammation, including IL-1β, IL-6, IL-8 and IL-10, CRP, TNFα, macrophage migration inhibitory factor, monocyte chemotactic protein-1, and NFκB activity. Measurement of insulin signaling in skeletal muscle and gene expression of inflammatory markers in adipose tissue will also be included as secondary outcome measures. Other outcome measures will include self-reported questionnaire data and nutrient analyses derived from dietary records.

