## Discussion

To the best of our knowledge, this is the first clinical trial supplementing a sufficient dose of vitamin D in vitamin D deficient individuals, employing gold-standard measures of insulin sensitivity and secretion, and comprehensively investigating mechanisms of action including chronic low-grade inflammation in human beings.

Insulin resistance is common in obesity and is a key pathogenic process underpinning type 2 diabetes. Interventions that reduce insulin resistance, including lifestyle, weight loss, and pharmacological therapies, prevent and treat type 2 diabetes [53]; however, to date they have failed to slow the increasing burden of insulin resistance and resultant type 2 diabetes. Type 2 diabetes currently affects approximately 1 million Australians and, if it continues to rise at the current rate, it is estimated that this number will increase to 3 million by 2025 [31]. Diabetes is a major cause of morbidity and mortality, primarily due to an increased risk of cardiovascular disease. Moreover, Australians with type 2 diabetes require healthcare, carers, and government subsidies totalling up to 6 billion dollars in healthcare costs annually. It is vital that additional effective primary prevention strategies are established to reduce insulin resistance and prevent and manage type 2 diabetes [31]. This trial will thus inform and advance this important field.

If vitamin D supplementation improves insulin sensitivity or secretion in this trial, then with large-scale interventions, treating vitamin D deficiency could become a mainstream strategy for diabetes prevention in overweight and obese individuals who are deficient in vitamin D. Vitamin D supplementation would offer a cost-effective and easily administered intervention that could have a considerable impact on health outcomes in Australia and worldwide. In addition, vitamin D could also play a role in counteracting adverse cardiovascular events, as well as improving underlying inflammatory responses, thereby decreasing risk factors associated with a range of metabolic conditions. High-quality clinical trials, such as this, are therefore an important first step towards elucidating the true potential of vitamin D supplementation in promoting health and well-being, and reducing insulin resistance and potentially the risk of type 2 diabetes and its associated comorbidities.

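### The abstract makes insulin sensitivity and secretion the primary outcome; the outcomes section and the sample size make it sensitivity alone

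*Protocol article*

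**What the plan says.** All statements are in the current text of the protocol article.

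- **Abstract, Background.** The primary aim is to find out whether raising 25(OH)D "will increase insulin sensitivity and insulin secretion".
- **Abstract, Methods/Design.** Measurements are repeated at follow-up, "with the primary outcome measure expressed as a change from baseline in insulin sensitivity and secretion". The next sentence gives the secondary outcomes: "Secondary outcome measures will compare changes in anthropometry, cardiovascular risk factors, and inflammatory markers". Secretion is not in that list.
- **Outcome measurements.** "The primary outcome measure in this trial is the difference (change) in insulin sensitivity between the vitamin D and placebo groups". It continues: "Secondary outcome measures include changes in insulin secretion, weight, body mass index", followed by the remaining secondary outcomes.
- **Sample size calculation.** The only calculation is for insulin-mediated glucose uptake, with mean 8.1 and SD 2.0 mg/kg/min and a 20% difference between arms. The error rates are stated thus: "Based on a type I error of 0.05 (two-tail) and a type II error of 0.20". The result is 25 completers per arm. No mean, SD or target effect is given for secretion.
- **Statistical analysis.** All tests are two-sided with a 0.05 threshold. No rule is given for combining two primary outcomes.

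**The concern.** The abstract's version is more than a loose phrase. It names both measures as primary and also leaves secretion out of its secondary list, which is consistent with treating secretion as primary. The Outcome measurements section says the opposite.

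The two measures come from different procedures. Sensitivity comes from the hyperinsulinemic euglycemic clamp. Secretion comes from the intravenous glucose tolerance test, as the average incremental insulin from the third to the fifth minute. They can disagree. With a neutral clamp and a nominally significant secretory response, one report could cite the abstract and present a primary finding, while another could cite the outcomes section and present a secondary one. At stake is which result answers the trial's question. A published protocol should settle that before the data are seen, and the Trial status section says the trial was still recruiting.

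**Working it through.** **Inputs.** From the Sample size calculation section: mean 8.1, SD 2.0, difference 20%, two-sided alpha 0.05, power 80%, 25 per arm. The SD is taken as the plan gives it. The correlation between the two outcomes and the effect on secretion are not given, so any value used for them below is an assumption.

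**1. The plan's own figure.** Difference = 0.20 × 8.1 = 1.62. Standardised effect = 1.62 / 2.0 = 0.81.

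- Normal approximation: n per arm = 2 × (1.960 + 0.842)² × (2.0 / 1.62)² = 23.9, so 24.
- Two-sample t-test: 24.92, so 25.
- Power at 25 per arm: 81.7% (normal) or 80.1% (t).

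The stated 25 per arm is reproduced for sensitivity as the sole primary outcome at 0.05.

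**2. Two primary outcomes, either one sufficient, each at 0.05.** For independent tests the family-wise error is 1 − 0.95² = 0.0975. With bivariate normal test statistics it falls as the correlation grows:

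| Assumed correlation | Family-wise error |
|---|---|
| 0 | 9.75% |
| 0.3 | 9.5% |
| 0.5 | 9.1% |
| 0.8 | 7.8% |
| 0.9 | 7.0% |

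Splitting alpha to 0.025 each would restore 5% overall. Power for sensitivity at 25 per arm would then be 70.8% (t), and 80% power would need 31 per arm (30.27 rounded up).

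**3. Two primary outcomes, both required, each at 0.05.** A false claim requires at least one true null hypothesis to be rejected at 0.05, so the type I error is at most 5% and no alpha split is needed. Joint power cannot exceed the 80.1% for sensitivity alone. If the outcomes are independent and secretion has the same standardised effect of 0.81, joint power is 0.801² = 0.642, about 64%. A positive correlation would raise this towards 80.1%; a smaller effect on secretion would lower it.

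**4. Comparison.** Sensitivity alone keeps both the stated 5% and the stated 80%. Under the assumptions shown, the either-suffices reading exceeds 5% (or loses power once alpha is split), and the both-required reading falls short of 80%.

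**The case against.** The strongest reply is that the body of the article already points one way. The section devoted to outcomes speaks of one primary outcome, names sensitivity, and lists secretion first among the secondary outcomes. The sample size is built on the same measure. On this view the abstract departs from a design that is otherwise coherent. That is largely right, and it is why the repair follows the outcomes section. It does not remove the conflict, because the article does not say which statement governs. The aim in the abstract's Background paragraph is weaker evidence, since an aim may be broader than an endpoint; the direct clash is between the abstract's Methods/Design paragraph and the Outcome measurements section.

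A reader might go further and infer that the trial's 5% error rate is unprotected. The document does not support that. The 9.75% requires that either outcome alone may carry the primary claim, and no section says so. The abstract joins the two with *and*, which can equally mean that both must succeed.

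A reader might also take the Discussion section, "If vitamin D supplementation improves insulin sensitivity or secretion in this trial", as an either-or success criterion. The sentence goes on to speculate about what such a result could mean for diabetes prevention. It sets no threshold or rule for declaring the trial positive.

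Nor is the lack of a multiplicity rule a defect in itself. Such a rule is commonly left to the statistical analysis plan, which is not at hand. A hierarchy set there would still leave this article contradicting itself.

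**Conclusion.** The point stands as an internal contradiction about the primary outcome: secretion is part of it in the abstract and secondary in the outcomes section. The sensitivity-only version is the one that the sample size supports, with 25 per arm and about 80% power.

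The statistical cost of the other version is conditional. It is a family-wise error of up to 9.75% if either outcome may count, or joint power of about 64% if both must succeed. The first figure assumes independent tests. The second assumes independent outcomes and an equal standardised effect on secretion. Neither is an established property of the trial, because the article states no rule for two primary outcomes. The contradiction still needs correcting, because it leaves open which result is the trial's answer.

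**What to change.** State clamp-measured insulin sensitivity as the single primary outcome throughout. In the abstract, reword the primary aim (Background) and the primary outcome sentence (Methods/Design) so that they refer to sensitivity only, and add insulin secretion to the abstract's secondary outcomes. Secretion should keep the rank that the Outcome measurements section gives it, a secondary outcome with no special status. Rewording the Discussion sentence to match is optional.

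The cost is wording only: 25 per arm, alpha 0.05 and all procedures are unchanged. The downside for the investigators is that a secretion result can no longer be presented as a primary success.

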**Discussion:**

The trial will provide much needed clinical evidence on the impact of vitamin D supplementation on insulin resistance and secretion and its underlying mechanisms, which are relevant for the prevention and management of type 2 diabetes.

**Trial registration:**

Clinicaltrials.gov ID: NCT02112721.

## Background

Vitamin D has well established endocrine functions in calcium absorption and healthy mineralization of bone as well as muscle function [1]. Low vitamin D levels have also been associated with many chronic diseases, including obesity [2], type 2 diabetes [3], cardiovascular disease [4], and cardiovascular and all-cause mortality [5]. However, knowledge gaps around vitamin D in these chronic diseases remain significant. This is increasingly clinically relevant today with vitamin D deficiency being prevalent worldwide as people adopt sedentary indoor lifestyles and use sunscreen and protective clothing to reduce the risk of skin cancer [1]. Diet is also not an ideal way to obtain vitamin D because few foods are naturally high in vitamin D and foods fortified with vitamin D are limited internationally [1]. The use of supplements offers a practical option for treating deficiency, while avoiding conflict with current public health measures for sun avoidance to protect against skin cancer [6]. However, the level of supplementation appropriate to improve vitamin D status remains controversial [7]. Currently, recommended daily oral intake is between 5 and 15 μg/day (200–600 IU/day) for adults (ages 19–70) [8, 9]. However, several recent studies suggested that an oral intake of at least 100 μg/day (4,000 IU/day) is required to raise serum concentrations of 25(OH)D to an optimal level within 2 to 3 months [10, 11]. Yet few existing studies have reached this level of replacement.

In relation to type 2 diabetes and cardiovascular risk factors, cross-sectional studies have shown that low plasma concentrations of 25(OH)D are associated with higher fasting serum glucose concentrations [12]; increased insulin resistance [13]; increased first and second phase insulin secretion [14, 15]; higher levels of haemoglobin A_1_c (HbA_1_c) [16, 17]; higher blood pressure [18, 19]; and higher levels of triglycerides and lower high-density lipoprotein cholesterol [20]. Prospectively, low serum concentrations of 25(OH)D have been associated with the development of insulin resistance [21], type 2 diabetes [22], hypertension [23], incidence of cardiovascular disease, and mortality [23–25]. Despite epidemiological data, there are relatively few good-quality interventional studies. Recent meta-analyses show significant heterogeneity in study quality, risk of bias, duration, dosages, and vitamin D deficiency status of participants, sample sizes, as well as surrogate measures of diabetes and cardiovascular disease, making it difficult to interpret study findings [23, 26]. In addition, many studies did not account for lifestyle factors, nor have they included dietary intake of vitamin D or calcium in their analyses, all of which affect both vitamin D levels and risk of type 2 diabetes and cardiovascular disease [23]. While recent evidence is limited and inconclusive, it does suggest that vitamin D might only have beneficial effects on vitamin D deficient individuals (25(OH)D < 50 nmol/l) who have received supplementation of sufficient dosages and durations, factors which require consideration in the design and execution of future trials.

Chronic low-grade inflammation is another factor that occurs in obesity. It is a risk factor for insulin resistance and many chronic diseases including type 2 diabetes and cardiovascular disease [27, 28]. There is evidence from *in-vitro* studies that vitamin D has anti-inflammatory properties [29–31]. However, there is a lack of human data [29].

While some large-scale trials are currently underway to assess the relationship between vitamin D and cardiovascular risk or disease [32], the role of vitamin D in insulin resistance or secretion and in regulating underlying chronic inflammation still needs to be assessed with good-quality trials and using gold-standard measures of glucose metabolism to address existing knowledge gaps [33].

To this end, we aim to perform a well-designed randomized placebo-controlled trial in healthy but overweight and obese individuals, as they are, on average, insulin resistant and have chronic low-grade inflammation. We aim to measure insulin sensitivity and secretion using gold-standard methodology, rather than examining glucose levels, HbA_1_c or using indirect measures of insulin sensitivity or secretion, which tend to change only slightly in nondiabetic individuals [23]. We will also measure blood pressure and lipid profile as surrogate measures of cardiovascular risk. Finally, chronic low-grade inflammation will be explored as a mechanism potentially linking low vitamin D levels and insulin sensitivity or secretion as well as cardiovascular risk factors.

## Methods/Design

### Study design and setting

This study is a parallel-group randomized placebo-controlled trial. The study design is presented in Fig. 1. Fifty overweight but otherwise healthy normoglycaemic adults aged between 18 and 60 years, and with serum concentrations of 25(OH)D between 25 and 50 nmol/l on screening will be enrolled. Participants will be randomized to receive either placebo or vitamin D supplementation (25 participants in each arm) for 16 weeks, with a goal of achieving optimal 25(OH)D levels of approximately 100 nmol/l. Those with severe deficiency (serum 25(OH)D levels below 25 nmol/l) will not be included in the current trial but will be allocated to a nonrandomized mandatory treatment group and studied before and after supplementation. Overweight and obese subjects will be selected for this study, as they are generally more insulin resistant and more sedentary, and have higher levels of inflammatory markers and lower levels of vitamin D, all of which are factors that increase the risk of type 2 diabetes [34, 35]. Participants will be sought out via several advertising strategies, including posters, flyers, newspapers, and email newsletters at Monash University and Monash Medical Centre in Melbourne, Australia, and via online advertising avenues, including social media and popular community websites. Interested participants will be informed that their participation is voluntary and that they can withdraw at any time, and they will also be asked to read the details of the study provided in an information pack. Once all concerns and questions have been addressed, participants will be asked to sign an informed consent form prior to commencing any tests.

**Fig. 1 Fig1:**
[figure not shown]
Trial protocol. DEXA, dual X-ray absorptiometry; FBC, full blood count; IVGTT, intravenous glucose tolerance test; LFT, liver function test; OGTT, oral glucose tolerance test; UEC, urea, electrolytes, creatinine

### Inclusion criteria

To take part in the trial, participants must be within the age range of 18 to 60 years inclusive, nondiabetic, and generally healthy, as determined by medical screening. Eligible participants must be overweight or obese (body mass index > 25 kg/m^2^). Their weight should not exceed 159 kg, owing to facility restrictions, and it should be stable, with a change of less than 5 kg in the preceding year. They should also have no intention to lose weight or change their diet or physical activity during the trial. To be included, individuals should also have a serum concentration of 25(OH)D of <50 nmol/l. However, those with frank vitamin D deficiency (<25 nmol/l) will not be randomized, but will instead be purposely allocated to the vitamin D group as allocation to placebo for 16 weeks might not be safe for these individuals.

### Exclusion criteria

Exclusion criteria will include smoking, high alcohol use (more than four standard drinks per week for men and more than two standard drinks per week for women), hypercalcemia, allergies, diabetes (previously diagnosed or on the basis of an oral glucose tolerance test), and the use of medication, including vitamins and other supplements. Based on medical history or physical or laboratory examination, participants will also be excluded if they have any kidney, cardiovascular, hematological, respiratory, gastrointestinal, endocrine or central nervous system diseases, as well as psychiatric disorders, active cancer within the preceding 5 years, or the presence of acute inflammation. Women who are experiencing menopause, pregnant, or lactating will also be excluded.

### Sample size calculation

Based on data from a similar healthy cohort of overweight or obese subjects in our metabolic laboratory, with a mean (standard deviation) insulin-mediated glucose uptake value of 8.1 (2.0) mg glucose per kg per minute, a sample size of 25 completing each arm is required to detect a 20 % change in insulin-mediated glucose uptake between treatment group and placebo. The 20 % increase is based on results from a study indicating the effect of vitamin D supplementation in subjects with diabetes using a comparable insulin sensitivity measurement technique and 4 weeks’ treatment [36]. Based on a type I error of 0.05 (two-tail) and a type II error of 0.20 (power = 80 %), we would require 50 participants to complete the trial.

### Screening

The study timeline is presented in Fig. 2. Female participants who are not taking contraceptives will be required to commence metabolic testing in the follicular phase and a urine pregnancy test will be performed to exclude pregnancy. At visit 1, a signed informed consent form will be obtained from each participant followed by screening by a registered medical practitioner, who will collect medical history and perform a physical examination, including measurement of blood pressure, height, body weight, and waist and hip circumference.

**Fig. 2 Fig2:**
[figure not shown]
Study timeline. IVGTT, intravenous glucose tolerance test; OGTT, oral glucose tolerance test

At the second visit, participants will undergo an oral glucose tolerance test with measurement of fasting and 2 hour glucose levels to exclude diabetes according to World Health Organization guidelines [37]. Blood samples will be sent to Monash Pathology services to be analyzed for serum concentration of 25(OH)D as well as full blood count, kidney and liver function tests, lipid profile, parathyroid hormone levels, and concentration of calcium, magnesium, phosphate, and C-reactive protein (CRP) as a marker of inflammation.

